**Fig. 2 Fig2:**
[figure not shown]
Overview of the study timeline for the birth companion intervention

### Study population

The study population will include: eligible women who give birth at participating facilities; birth companions of eligible women; all eligible providers working in the ANC, and labor, birth, and postpartum wards; and unit managers who work in the facilities during the study period. Inclusion and exclusion criteria are shown in Table 4.

**Table 4 Tab4:** Inclusion and exclusion criteria for facilities and study participants

Participant	Inclusion	Exclusion
Health facilities	• Prior to randomization, head of facility grants permission for facility to participate in the study • Be willing to develop, adopt, and implement the birth companion standard operating procedures and other components of the birth companion intervention package • Have 16 to 30 births minimum per month during the past three months • Be in the Addis Ababa and surrounding area of Ethiopia; Machakos or Murang’a County of Kenya; or Kano or Nasarawa States of Nigeria	• Facility staff strike or other disturbance to routine care noted prior to randomization that would pose significant challenge(s) to achieving the study objectives
Providers	• At the time of enrollment, work in antenatal care and/or labor and birth ward(s) of study facility • Able and willing to provide informed consent to participate in the study	
Mothers	• Per participant report, age 15 years or older • Have a vaginal birth • Able and willing to provide informed consent to participate in the study	• Unable to participate in an interview due to their physical or emotional condition (e.g., caused by an adverse birth outcome) • Unable to provide valid information because of mental or other serious health condition
Birth companions	• For emancipated minors, age 15 years or older. If not an emancipated minor, 18 years or older. Age per participant report • Person was present at labor and/or birth • Identified as a birth companion by the birthing mother • Willing and able to provide informed consent to participate in the study	• Unable to provide valid information because of mental or other serious health condition
Unit managers	• Involved in the implementation and management of the birth companion intervention • Able and willing to provide informed consent to participate in the study	

### Sample size

#### Quantitative

The sample size justification is based on estimating coverage of birth companionship. We assumed a within-facility intra-class correlation coefficient (ICC) between 0.05 and 0.5 (higher is more reasonable). We also assumed post-birth companion support coverage at 50%. Baseline/standard practice birth companion coverage varied between 5% and 20%.

Sample size is calculated separately by country for two-sample comparison of proportions (with pooled Z-test) in a cluster randomized design using PASS (PASS 15 Power Analysis and Sample Size Software (2017). NCSS, LLC. Kaysville, Utah, USA, ncss.com/software/pass) [25].

The calculations below apply to the study area in Ethiopia, the two study counties in Kenya, and the two study states in Nigeria. We assume the same baseline level of birth companion coverage in all three countries. There are the same total number of facilities to be randomized at each study area, n = 12 (three in the standard arm and nine in the intervention arm). There will be a total of 12 facilities in Ethiopia, 24 in Kenya, and 24 in Nigeria.

The number of women per facility and total number of women across the two study arms per study site needed was calculated for at least 80% statistical power to test differences in proportions of birth companion coverage between study arms at 0.05 level of statistical significance, assuming that for every three facilities randomized to the birth companion intervention, one facility will be randomized to the standard practice arm and a coefficient of variation of one. Post-birth companion intervention coverage is assumed to be 50%.

Conservatively assuming 20% birth companion coverage in the standard practice (control) arm and 50% in the birth companion intervention arm at the endline, to have 80% statistical power to detect this difference in proportions at 0.05 level of statistical significance, coefficient of variation of one, we will need to include 62 women who recently gave birth (on average) at each of the 12 health facilities per study area, for a total of approximately 744 women across the two study arms (186 in control arm, 558 in the intervention arm). In this scenario in each of the study sites (Addis Ababa and surrounding area, Machakos and Murang’a counties, and Nasarawa and Kano states), three facilities will be randomized to the standard arm, and nine facilities to the birth companion intervention arm. Since the coefficient of variation is almost one, based on the facility data presented in Tables 1, 2 and 3, the same sample size is used for considering a varying cluster size. We will include all births occurring within the seven data collection days from all facilities. Thus, we will recruit more births from health facilities with a higher volume of births and fewer from health facilities with smaller volume of births. Randomization of facilities was conducted by the Johns Hopkins Biostatistics Center.

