The evidence that birth companionship improves labor outcomes and experience of care has been available for many years. As such, global guidance supports birth companions. The World Health Organization (WHO) states “continuous companionship during labor and childbirth is recommended for improving women’s satisfaction with services;” [14] and a companion of choice is recommended for all women throughout labor and childbirth [15]. The WHO quality of care framework also states that a woman should have access to the social and emotional support of her choice [16]. National polices in Ethiopia, Kenya, and Nigeria support birth companions. However, birth companions are not yet incorporated into routine practice, and women typically labor and give birth alone [11, 12, 17–23]. One study in Ethiopia showed that 98% of women were not allowed to have a birth companion, and another study in Kenya found 78% were not allowed a companion during labor and 84% during delivery [17, 19]. In Nigeria, a study showed that only 29% of mothers experienced companionship during delivery [20].

A 2019 Cochrane review outlined common barriers to facilities adopting birth companionship: health facility policies, provider attitudes, facility infrastructure, and preparation of families and birth companions [24]. Implementation research on birth companions is needed to test interventions in varying clinical settings and cultures that will address these barriers and lead to increased uptake of birth companions in health centers and hospitals. Common barriers identified in the literature that hinder birth companion presence include lack of facility polices, low knowledge of the benefits of birth companionship by providers and families, space and privacy constraints, negative attitudes of providers, and lack of preparedness of families and birth companions [24]. It is unknown whether a health facility’s readiness to change impacts their ability to successfully implement interventions that increase uptake of birth companions [10].

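### The stated 80% power per site holds only near the bottom of the plan's own ICC range of 0.05 to 0.5, and the ICC behind it is not named

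*Protocol article*

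**What the plan says.** All design inputs are in the Protocol article under Sample size, Quantitative.

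- ICC: "We assumed a within-facility intra-class correlation coefficient (ICC) between 0.05 and 0.5 (higher is more reasonable"). No single value is chosen from this range.
- Test: "two-sample comparison of proportions (with pooled Z-test) in a cluster randomized design using PASS".
- Facilities per site: "n = 12 (three in the standard arm and nine in the intervention arm").
- Target: the number of women "needed was calculated for at least 80% statistical power to test differences in proportions of birth companion coverage between study arms".
- Scenario: "Conservatively assuming 20% birth companion coverage in the standard practice (control) arm and 50% in the birth companion intervention arm at the endline". The plan's control range is 5% to 20%.
- Result: "we will need to include 62 women who recently gave birth (on average) at each of the 12 health facilities per study area". The total is 744 per site, 186 control and 558 intervention. The power claimed for this number is 80% at a 0.05 level, with the coefficient of variation set to one.

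The same section says that facility sizes in Tables 1 to 3 have a coefficient of variation close to one, and that the sample size therefore also serves for unequal clusters. Under Analysis of primary outcomes, the primary analysis is done separately for each sub-national region. Each primary test therefore has 12 facilities.

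**The concern.** With three control facilities, power depends mainly on the ICC. The plan allows a tenfold range for it, says that higher values are the more plausible ones, and then gives one power figure with no ICC attached. A reader will take 80% as a property of the design across the assumptions just listed.

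If the figure belongs to the low end of the range, each of the five site-level primary tests could easily miss the planned 30-point difference. A non-significant site result, read against a claimed 80%, would then look like evidence against the package when it says little either way.

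**Working it through.** **Inputs from the plan.** m = 62 women per facility; 3 and 9 facilities; p1 = 0.20, p2 = 0.50; alpha 0.05; coefficient of variation (CV) of facility size 1; ICC ρ from 0.05 to 0.5. *Assumption:* the test is two-sided, because sidedness is not stated.

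**Formulas.**
- Usual design effect: DE = 1 + ((1 + CV²)m − 1)ρ. With equal facilities this is 1 + (m − 1)ρ.
- Relative-efficiency alternative: DE = (1 + (m − 1)ρ) / (1 − CV²λ(1 − λ)), with λ = mρ/(mρ + 1 − ρ).
- Effective sizes: n1 = 186/DE, n2 = 558/DE.
- Pooled proportion: (186 × 0.20 + 558 × 0.50)/744 = 0.425.
- SE0 = √(0.425 × 0.575 × (1/n1 + 1/n2)); SE1 = √(0.16/n1 + 0.25/n2).
- Pooled-Z power = Φ((0.30 − 1.96·SE0)/SE1). The unpooled version uses SE1 in both places.

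**Reproducing the stated figure.** Two routes reach it.
- (a) CV 1, ρ = 0.05: DE = 1 + 123 × 0.05 = 7.15; n1 = 26.0, n2 = 78.0; SE0 = 0.1119, SE1 = 0.0967; power Φ(0.834) = 79.8%. Exactly 80% needs m = 65.
- (b) Equal facilities, ρ = 0.10: DE = 1 + 61 × 0.10 = 7.10; n1 = 26.2, n2 = 78.6; SE0 = 0.1115, SE1 = 0.0964; power Φ(0.845) = 80.1%. The smallest m reaching 80% is exactly 62.

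Under (b) the stated CV of one was not applied. Applying it at ρ = 0.10 gives DE = 1 + 123 × 0.10 = 13.3, n1 = 14.0 and power Φ(0.006) = 50.3%. The facility sizes in Tables 1 to 3 do vary: the CV is 1.09 in Ethiopia, 1.12 in Machakos, 1.01 in Murang'a, 0.74 in Kano and 0.99 in Nasarawa.

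**Power (%) across the plan's range, m = 62, 20% against 50%, two-sided**

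| Variant | ICC 0.05 | 0.10 | 0.15 | 0.20 | 0.30 | 0.50 |
|---|---|---|---|---|---|---|
| CV 1, pooled | 79.8 | 50.3 | 34.9 | 26.5 | 17.9 | 11.1 |
| CV 1, unpooled | 87.3 | 62.3 | 46.8 | 37.4 | 27.0 | 18.1 |
| Relative efficiency, pooled | 92.9 | 74.8 | 59.2 | 48.0 | 34.0 | 21.1 |
| Relative efficiency, unpooled | 96.2 | 83.5 | 70.6 | 60.1 | 45.8 | 31.1 |
| Equal facilities, pooled | 96.8 | 80.1 | 63.1 | 50.6 | 35.2 | 21.5 |
| Equal facilities, unpooled | 98.5 | 87.6 | 74.0 | 62.7 | 47.1 | 31.5 |

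At ICC 0.50 with CV 1, DE = 1 + 123 × 0.50 = 62.5, so the 186 control women carry the information of about 3 independent women. The stretch from 0.15 to 0.50, where no row reaches 80%, is 0.35/0.45 = 78% of the assumed range.

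**Would more women help?** With unlimited women and equal facilities, n1 tends to 3/ρ. Pooled power is then at most 67.4% at ICC 0.15, 53.5% at 0.20 and 21.8% at 0.50; unpooled, the ceiling at 0.15 is 77.6%. At these ICCs the limit is the number of facilities.

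**Control coverage of 5% instead of 20%** (CV 1, pooled): above 99% at ICC 0.05, 94.6% at 0.10, 62.0% at 0.20 and 18.4% at 0.50. The plan ties 62 women to the 20% scenario.

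**The case against.** Several points limit what can be said.

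- *A reader might infer that 62 was computed at ICC 0.05 and that the most favourable value was picked.* The document does not establish this. Route (b) reproduces 62 exactly at ICC 0.10, and the remark that the same sample size serves for varying cluster size can be read as an equal-cluster figure carried over.
- *A reader might infer that no number of women gives 80% once the ICC passes about 0.06 or 0.07.* That follows only from the usual design effect with CV 1. With equal facilities or the relative-efficiency correction, unlimited women give 85.6% at ICC 0.10 (pooled). The article plans a cluster-weighted test without giving the weights, so the least efficient formula cannot be presumed.
- *The word conservatively.* It describes 20% control coverage, the least favourable end of the 5% to 20% range, and is correct there. It makes no claim about the ICC.
- *The Background figure for Nigeria.* "In Nigeria, a study showed that only 29% of mothers experienced companionship during delivery" is one study of delivery only, not tied to Kano or Nasarawa. It does not show that 20% is wrong. At 29% control coverage (CV 1, pooled) power would be 46.0% at ICC 0.05 and 26.4% at 0.10, which is useful only as a sensitivity.
- *Sidedness.* A one-sided 0.05 test helps: some unpooled variants then reach 80% at ICC 0.15. None does at 0.20, whatever the number of women.
- *Country-level testing.* The sample size is said to be calculated by country, and 6 against 18 facilities in Kenya or Nigeria would do better: at ICC 0.20, 52.0% (CV 1) to 83.2% (equal facilities), pooled. But the primary analysis is specified by sub-national region.
- *Condensation.* The full protocol may name the ICC. That would settle which route was used. It would not reconcile one unqualified 80% with the printed range and its stated preference for higher values.

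**Conclusion.** The point holds in this form: at 20% control coverage the stated 80% is true only near the bottom of the assumed ICC range, around 0.05 with the stated CV and usual design effect, or 0.10 with equal facilities. It fails at 0.15 and above in every two-sided variant computed. Across the six variants, power is 26.5% to 62.7% at ICC 0.20 and 11.1% to 31.5% at ICC 0.50. This applies to each site-level primary test.

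The conclusion rests on a two-sided 0.05 level, the normal approximation, 62 women per facility and 20% against 50%. The exact ICC at which 80% is lost depends on the cluster-size formula. The shortfall over most of the range does not. At 5% control coverage the shortfall is much smaller, but at ICC 0.50 the CV 1 pooled figure is still only 18.4%.

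The power statement should be corrected, since it conflicts with assumptions printed in the same section.

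**What to change.** 1. Name the ICC and the cluster-size formula that produced 62, and say whether the CV of one entered the calculation. The sponsor must supply the value; it should not be inferred from either route above. State the sidedness of the test.
2. Replace the single 80% with a table of per-site power at ICC 0.05, 0.10, 0.20 and 0.50, for control coverage of 5% and 20%, with 29% as an optional sensitivity.
3. State that at 20% control coverage each site's test is under-powered over most of the assumed ICC range, so a non-significant site result is not evidence of no effect.
4. Keep *conservatively* for the control coverage only, and say that it does not extend to the ICC.

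The cost is some wording and one table, with no extra women or facilities. The price is a less favourable power statement.

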**Methods:**

This two parallel arm cluster randomized controlled trial will evaluate the impact of a targeted intervention package on scale-up of birth companionship at public sector health facilities in Ethiopia (five study sites encompassing 12 facilities), Kenya (two sites encompassing 12 facilities in Murang’a and 12 facilities in Machakos counties), and Nigeria (two sites encompassing 12 facilities in Kano and 12 facilities in Nasarawa states). Baseline and endline assessments at each site will include 744 women who have recently given birth in the quantitative component. We will interview a maximum of 16 birth companions, 48 health care providers, and eight unit managers quarterly for the qualitative component in each country.

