**Nasarawa**			
1	312	CEmONC	
2	300	CEmONC	
3	135	BEmONC	
4	109	CEmONC	
5	69	CEmONC	
6	64	BEmONC	
7	45	CEmONC	
8	41	CEmONC	
9	37	BEmONC	
10	37	BEmONC	
11	37	CEmONC	
12	36	BEmONC	

We will use a mixed methods approach to assess impact of the birth companion intervention package and measure the study outcomes with exit interviews, health facility register data extraction, in-depth interviews (IDIs), focus group discussions (FGDs), and key informant interviews (KIIs).

There are five data collection periods. We will first conduct a baseline assessment over the course of approximately four weeks, in facilities meeting the inclusion criteria. Health facilities that decline to participate in the study will be replaced by another facility. Facilities will be randomized after the baseline survey in a 3:1 ratio (i.e., for every three facilities that implement the birth companion intervention, one will serve as a control facility). Randomization is stratified by the number of facility deliveries and by country (Ethiopia) or by county or state within a country (Kenya and Nigeria). Intervention facilities will prepare to introduce the birth companion intervention package over the course of approximately two months to facilitate the presence of birth companions during labor, birth, and the postnatal period. Control facilities will continue to provide the local standard of routine care which may or may not include a birth companion. Facilities will not be replaced or reallocated to study arm post-randomization. This study does not place restrictions on facilities or participants regarding participation in other interventions or research.

We will have three quarterly quantitative and qualitative data collection periods, each lasting for approximately one week. We will conduct an endline quantitative survey, approximately 12 months after birth companion intervention initiation. Mothers, birth companions, health care providers, and unit managers in study facilities will have the option to decline to participate in the study.

At the end of the study, control facilities will be supported to implement the birth companion intervention package by staff from an intervention facility that has a birth companion coverage of approximately 50% or higher (see Fig. 2), assuming that one is available. We will provide limited technical and material support during this period.

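### The seven-day census of births cannot supply the 744 women per site on which the endline power rests; one of the two statements must change

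*Protocol article*

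**What the plan says.** All references are to the protocol article.

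- **Target.** Under Sample size, Quantitative: "we will need to include 62 women who recently gave birth (on average) at each of the 12 health facilities per study area". Over a whole site this comes to about 744, with 186 women in control facilities and 558 in intervention facilities. The premise is "Conservatively assuming 20% birth companion coverage in the standard practice (control) arm and 50% in the birth companion intervention arm at the endline". The calculation aims at "80% statistical power to detect this difference in proportions at 0.05 level of statistical significance, coefficient of variation of one".
- **Recruitment rule.** In the same paragraph: "We will include all births occurring within the seven data collection days from all facilities". The sentence names no data collection round. The next one uses the rule to explain why larger facilities will contribute more women.
- **Where 744 applies.** Abstract, Methods: "Baseline and endline assessments at each site will include 744 women who have recently given birth in the quantitative component".
- **Round lengths.** Design and setting says: "We will first conduct a baseline assessment over the course of approximately four weeks". Each of the three quarterly rounds lasts about one week. Endline is placed about 12 months after the intervention starts, and its length is not given.
- **Who counts.** Table 4 restricts mothers to those who "Have a vaginal birth", are at least 15, can be interviewed and consent.

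**The concern.** A sample size and a recruitment rule given in one paragraph should agree. Here the tables of facility volume allow a direct check, and they do not. The comparison at the end of the intervention is the primary analysis, and it is run separately for each sub-national region, so a busy site cannot make up for a quiet one. If endline were run as the sentence reads, each site would have well under half of the women on which its power was computed. If endline is meant to last longer, a reader cannot tell this from the text, and field teams could take seven days as the rule.

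**Working it through.** **Inputs.** Monthly births per facility from Tables 1 to 3; 62 women per facility; 3 control and 9 intervention facilities per site; 20% against 50%; pooled Z-test at 0.05. Two-sided testing is assumed, because the sidedness is not stated. The ICC is given only as a range, 0.05 to 0.5, and the value behind 744 is not stated. A month is taken as 30.4 days.

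**Step 1: reproduce the plan's figure.** 12 × 62 = 744; 3 × 62 = 186; 9 × 62 = 558.

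For power, let m be the mean number of women per facility. The design effect is DE = 1 + ((CV² + 1)m − 1) × ICC, and the effective control-arm size is n = 3m/DE. With pooled proportion (0.20 + 3 × 0.50)/4 = 0.425,

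power = Φ{[0.30 − 1.96 √(0.425 × 0.575 × (4/3)/n)] / √((0.16 + 0.25/3)/n)}.

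- ICC 0.10, equal clusters (CV 0): DE = 1 + 61 × 0.10 = 7.10, n = 186/7.10 = 26.2, power 0.801. The smallest m that reaches 80% is exactly 62.
- ICC 0.05, CV 1: DE = 1 + 123 × 0.05 = 7.15, n = 186/7.15 = 26.0, power 0.798. The smallest m that reaches 80% is 65.

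So 744 is reproducible as a figure for about 80% power under either pair of assumptions. The text does not say which was used.

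**Step 2: what seven days bring.** Births = monthly total × 7/30.4. Days to 744 births = 744/monthly total × 30.4.

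| Site | Births per month | Births in 7 days | Share of 744 | Mean per facility | Days to 744 births |
|---|---|---|---|---|---|
| Ethiopia | 1113 | 256 | 34% | 21 | 20 |
| Machakos | 904 | 208 | 28% | 17 | 25 |
| Murang'a | 1206 | 278 | 37% | 23 | 19 |
| Kano | 1384 | 319 | 43% | 27 | 16 |
| Nasarawa | 1222 | 281 | 38% | 23 | 19 |

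A 30- or 31-day month moves the range only to 204–323.

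These are counts of all births. The documents give no caesarean share. If it were 10% to 30% (an assumption), seven days would bring about 146 to 286 vaginal births per site, before refusals.

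**Step 3: what four weeks would bring.** In Machakos, 904 × 28/30.4 = 833 births, so 744/833 = 89% of all births would have to be eligible, reached and consenting. The same share is 73% in Ethiopia, 67% in Murang'a, 66% in Nasarawa and 58% in Kano.

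**Step 4: power at the seven-day yield.** The same formula, with m from the table above (range from Machakos to Kano):

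| ICC | Cluster-size CV | Power at m = 62 | Power at 7-day m |
|---|---|---|---|
| 0.05 | 0 | 97% | 84–91% |
| 0.05 | 1 | 80% | 66–72% |
| 0.10 | 0 | 80% | 67–73% |
| 0.10 | 1 | 50% | 43–46% |
| 0.20 | 1 | 26.5% | 24.5–25.4% |
| 0.50 | 1 | 11% | 11% |

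Worked example, Machakos at ICC 0.05 and CV 1: m = 17.3, DE = 1 + (34.7 − 1) × 0.05 = 2.68, n = 52.0/2.68 = 19.4, power 0.66.

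**The case against.** The strongest reply is that the seven-day sentence describes the quarterly rounds. It names no round, Design and setting gives exactly those rounds about a week, and the Abstract assigns 744 to baseline and endline only. Trial status supports this: the baseline survey ran from October 10 to November 22, 2022 in Ethiopia (44 days) and from November 1 to December 9 in Kenya (39 days), so a survey with the 744 target was not run as a seven-day census. A condensed article may also leave the endline length to the full protocol.

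Much of this stands. A reader might infer that endline is a seven-day survey and that the trial is therefore underpowered. The documents do not say that. But the reply does not remove the contradiction: the sentence stands inside the derivation of the endline sample, is not limited to any round, and is the only window attached to that sample.

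A second reply is that lost women cost little power, because three control facilities per site dominate the variance. This is correct at higher ICCs, and the protocol itself calls higher values more reasonable. A reader who takes 28–43% of the women to mean a proportionate loss of power would be wrong. Nor is the fall from 80% to 66–72% general: it holds at ICC 0.05 with CV 1, while equal clusters at ICC 0.05 still give 84–91% in seven days.

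The Machakos margin in Step 3 assumes exactly 28 days. Four weeks is stated as approximate and the Kenya baseline lasted longer, although the dates are not given by county.

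Finally, the phrase about all births might look like a conflict with the vaginal-birth criterion. Data collection, Quantitative, already limits interviews to women who meet the eligibility criteria. Caesareans matter here only because they lower the yield further.

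**Conclusion.** The contradiction is real and follows from the protocol's own tables. About 744 women per site and a seven-day census cannot both hold, because seven days bring about 208 to 319 births per site, at most 28% to 43% of the target. Reaching 744 births takes about 16 days in Kano to 25 in Machakos before any exclusion. The yields rest only on the tabulated volumes and the days in a month.

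Whether this is a wrong sentence or a real shortfall cannot be settled from the article, because the endline length is not stated. If endline runs about four weeks, the defect is one misleading sentence. If it runs seven days, the stated size is not delivered, and power is about 66–73% under the two sets of assumptions that reproduce 744. At higher ICCs, power is far below 80% with either window. That is a separate matter which a longer endline would not cure.

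**What to change.** Choose one of two corrections.

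1. If endline is meant to reach 744: limit the seven-day sentence to the three quarterly rounds and state fixed baseline and endline windows long enough for 744 eligible women. About four weeks would do on these volumes, with Machakos checked separately because of its thin margin. A fixed common window keeps the plan's intention that recruitment follows facility volume.
2. If endline really is seven days: replace 744 by the expected yield, at most about 210 to 320 per site, and restate the power for it.

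In either case, state the ICC and the cluster-size assumption behind the figure, and bring the Abstract, Design and setting, and Sample size into line. The cost is a sentence or two. Only if endline had truly been planned at seven days and 744 is kept would it also need about two to three more weeks of data collectors.
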